##### Cardiorespiratory fitness

Given this study will recruit some high-risk participants (obesity class I: BMI 30–30.9 kg/m^2^, obesity class II: BMI 35–39.9 kg/m^2^ and obesity class III: BMI ≥ 40kg/m^2^) [51, 54] and in order to protect participant safety, a submaximal graded walking treadmill (make: h/p/cosmos; model: quasar) test will be conducted and used to estimate VO_2_ max. Guided by the Balke-Ware protocol for females [55], participants will warm-up for 4 min starting at a speed of 3.2km/hr and an incline of 0% and progressing to 3.8km/h by the end of the warmup, in line with the speed recommended for adults with obesity in the modified Balke protocol [56] With the speed remaining consistent, the gradient will then be increased by 2.5% every 3 min up until a gradient of 25%. If the participant has not achieved any of the criteria for test termination at this stage, the speed of the treadmill will then be increased by 0.3km/h every 3 min until they do so. The test will be deemed complete and terminated once the participant reaches 85% of their age-predicted HR_max_. Alternatively, the test will be terminated before the participant reaches 85% of age-predicted HR_max_ if (i) they report a rating of perceived exertion (RPE) ≥ 18 or (ii) reach volitional exhaustion. An RPE cut-off was included as a potential reason for test termination given that RPE ≥ 17–19 has both been utilised as a criterion for achieving VO_2_ max [57] and previously as a criterion for the termination of a submaximal Balke treadmill protocol in a clinical population [58, 59]. Furthermore, research indicates that RPE > 17 reasonably correlates with VO_2_ max and can be used to predict VO_2_ max with acceptable accuracy [60].

VO_2_ max will be estimated using the Fitness Registry and the Importance of Exercise National Database (FRIEND) equation (VO_2_ max = speed × (0.17 + fractional grade × 0.79) + 3.5) [61]. Gas exchange including O2 and CO2 concentrations, and respiratory exchange ratio (RER) will be measured using a gas analysis system (make: COSMED; make: Quark CPET, Rome, Italy). Heart rate will be measured every minute throughout the test by a heart rate monitor (make: Polar; model: Wind with WearLink chest belt). As CRF is being measured using a sub-maximal protocol, electrocardiograms will not be used during testing. Rating of perceived exertion (RPE) will be measured using the Borg RPE scale every minute of the test [62].

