##### Subjective self-report questionnaires

All participants will be issued a combined set of valid and reliable self-reported outcome questionnaires detailed in Table 2. These will take approximately 30 min to complete. The participant will be given the option to complete these surveys online or in paper format. Participants who wish to complete the questionnaires online will be sent an email with the link and the option to complete them either in advance or following their appointment in ISH. The self-reported measures are in line with the core outcome set for weight management interventions in adults with obesity [63, 64]. In addition, pain was included as an outcome given the strong association between chronic pain and obesity and the potential impact of pain on exercise adherence [65, 66].

**Table 2 Tab2:** Primary and secondary outcome measures

Outcomes	Measure(s)
Anthropometrics	BMI, body weight, % body fat, waist circumference, fat-free mass, lean mass, waist hip ratio, height
Cardiorespiratory Fitness	Predicted VO_2_ max
Muscle strength	5RM bench press, leg dynamometry, grip strength
Pain	Brief Pain Inventory (Short form)
Health-related quality of life	EuroQol-5D-5L (EQ-5D-5L) questionnaire
Mood	Patient Health Questionnaire-9 (PHQ-9)
Self-reported physical activity & sedentary time	International Physical Activity Questionnaire (IPAQ) (Short Form)
Sleep	Pittsburgh Sleep Quality Index

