#### Sample size

As this is a pilot study, which has the primary goal of evaluating the feasibility of the interventions and not ensuring there is adequate power to detect between-group differences, a formal sample size calculation is not required [48]. However, the researchers recognise that the sample size will need to be large enough to provide a degree of accuracy around the estimated effect of the interventions on a desired outcome (i.e. between-group difference in CRF which would be the primary outcome in an RCT) which would indicate whether a definitive RCT is worth pursuing. We estimated that we would need to recruit approximately 10% of the number of participants needed for a full-scale RCT. Based on previous research in this area [67], a sample size calculation for a definitive RCT indicates that we would need to recruit 484 participants. Therefore, allowing for 20% attrition, we aim to recruit 60 participants for this pilot study to inform the power analysis for a full-scale RCT.

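### The CRF outcome is called predicted VO2 max, but a speed-and-grade equation with no described extrapolation is applied to a test stopped early on mixed criteria

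*Protocol article*

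**What the plan says.** All the relevant text is in the protocol article.

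- **Test.** Cardiorespiratory fitness section: "a submaximal graded walking treadmill" test is run to estimate VO2 max. It is "terminated once the participant reaches 85% of their age-predicted HR_max", or before that point if "they report a rating of perceived exertion (RPE) ≥ 18 or (ii) reach volitional exhaustion".
- **Equation.** Same section: the estimate "will be estimated using the Fitness Registry and the Importance of Exercise National Database (FRIEND) equation", printed as "VO_2_ max = speed × (0.17 + fractional grade × 0.79) + 3.5".
- **Other data from the same test.** Heart rate and RPE are recorded every minute. In addition, "Gas exchange including O2 and CO2 concentrations, and respiratory exchange ratio (RER) will be measured". No role in deriving the outcome is described for any of these.
- **Reason for the RPE cut-off.** The section points to the use of high RPE as a criterion that VO2 max has been achieved, and says high RPE can predict VO2 max acceptably.
- **Label and role.** Table 2 gives "Predicted VO_2_ max" as the only CRF measure. The Sample size section speaks of the "between-group difference in CRF which would be the primary outcome in an RCT", and the aims include collecting data for that trial's power calculation.

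**The concern.** The printed equation has no heart-rate, age or RPE term. It converts a workload into an oxygen cost, so it gives VO2 max only if the workload entered is a maximal one. The main stopping rule is designed to prevent a maximal workload, and the article describes no step from the submaximal workload to the maximum.

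The alternative stops add a second problem. By the article's own rationale, a stop at RPE ≥ 18 signals near-maximal effort, while a stop at 85% of predicted HRmax does not. Both feed the same formula under the same label, so two women who stop at the same stage get the same score whatever effort it represented.

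CRF is what the interventions target and is the planned primary outcome of the definitive trial. At stake are the level and SD of CRF handed to that trial's sample size calculation, and the meaning of a pre–post change when the stopping reason differs between visits.

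**Working it through.** The plan gives no figure of its own to reproduce here. The check evaluates its equation on its own treadmill schedule and compares the result with a simple extrapolation to maximum.

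**Inputs from the Cardiorespiratory fitness section.** Speed is 3.8 km/h until 25% grade. Grade rises 2.5% every 3 min. After that, speed rises 0.3 km/h every 3 min. The main stop is 85% of age-predicted HRmax. Ages 18–50 come from Table 1.

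**Assumptions not in the article.** Speed enters in m/min (in km/h, a 12.5% grade would give 3.8 × 0.26875 + 3.5 = 4.5, barely above the constant). HRmax = 220 − age. Resting heart rate is 60–80 bpm. The percentage of heart-rate reserve equals the percentage of VO2 reserve.

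**Step 1: what the equation can return.** 3.8 km/h = 63.33 m/min.

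| Grade | Result (mL/kg/min) |
|---|---|
| 0% | 14.3 |
| 7.5% | 18.0 |
| 10% | 19.3 |
| 12.5% | 20.5 |
| 15% | 21.8 |
| 25% | 26.8 |

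One grade stage adds 63.33 × 0.79 × 0.025 = 1.25. Once 25% grade is reached, one speed step adds 5 m/min × (0.17 + 0.25 × 0.79) = 5 × 0.3675 = 1.84.

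**Step 2: fraction of reserve at a heart-rate stop.** f = (0.85·HRmax − HRrest)/(HRmax − HRrest).

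- Age 18, resting 60: (171.7 − 60)/(202 − 60) = 0.787
- Age 34, resting 70: (158.1 − 70)/(186 − 70) = 0.759
- Age 50, resting 80: (144.5 − 80)/(170 − 80) = 0.717

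**Step 3: shortfall.** Extrapolated VO2 max = 3.5 + (VO2 at stop − 3.5)/f.

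| Case | Stop at | Equation | Extrapolated | Shortfall |
|---|---|---|---|---|
| Age 18, rest 60 | 10% | 19.3 | 23.5 | 18.2% |
| Age 34, rest 70 | 12.5% | 20.5 | 25.9 | 20.8% |
| Age 50, rest 80 | 15% | 21.8 | 29.0 | 24.9% |

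For stops at 10–15% grade the shortfall is therefore about 18–25%. At 12.5% grade, an equation value of 20.5 goes with an extrapolated 25.1–27.3.

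**Step 4: mixing.** Take two women who both stop at 12.5% grade and so both score 20.5. If one stopped on heart rate, her VO2 max is about 25–27 on these assumptions. If the other stopped at exhaustion, hers may be close to 20.5. The score cannot tell them apart.

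**Step 5: a changed stopping reason with unchanged VO2 max.** A woman who stops on RPE at 10% at baseline, and at follow-up continues to the heart-rate limit at 12.5%, shows a gain of 20.5 − 19.3 = 1.25 (unrounded). The reverse order shows a loss of 1.25. If her heart rate at a given workload happens to be lower at follow-up, a heart-rate stop at baseline can become an RPE stop at a higher stage, again an apparent gain. The sign is not fixed, and the size comes in whole stages.

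**The case against.** - **The workload entered is not stated.** The article never says in words that terminal speed and grade go into the equation. A condensed article may leave scoring to the full protocol. This stands as a limit on certainty: a reader might infer that heart rate and gas exchange are definitely unused, but the text only fails to describe a use. If an extrapolation exists, however, the derivation as printed is incomplete and still needs correcting.
- **Workload at a fixed heart rate is a usable fitness index.** This stands. The same test is used at both visits in randomised arms. If everyone stops on heart rate, scores shrink by a roughly common factor (0.72–0.79 of reserve here), mean difference and SD shrink together, and the standardised effect is largely preserved, especially if the definitive trial uses the same test. The harm arises when stopping reasons change between visits or differ by arm, or when the pilot's figures are read as VO2 max. The article gives no basis for estimating how often stopping reasons will change.
- **The bias has no single direction.** A reader might infer that every participant's level is understated by 18–25%, or that a changed stopping reason always inflates the gain. Neither follows. The shortfall applies to heart-rate stops only, and Step 5 shows movement both ways. Nor does the article support a large upward jump for a woman whose predicted HRmax is correct and whose heart-rate response is unchanged: the RPE stop counts only if it comes before the heart-rate limit.
- **CRF is secondary.** The pilot's primary aim is feasibility and acceptability, and it is expressly not powered for group differences. This limits severity, not correctness.

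**Conclusion.** The derivation is wrong as written and should be fixed, but it does not threaten the pilot's primary feasibility aim. An equation in speed and grade alone, fed by a submaximal test with no described extrapolation, does not yield VO2 max. It also pools heart-rate stops with stops that may be near-maximal.

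The structural defect rests on the printed equation and stopping rules, plus the natural reading that terminal workload is entered. The 18–25% shortfall is illustrative, covers heart-rate stops only, and depends on the outside assumptions listed. The step sizes of 1.25 per grade stage and about 1.84 per speed step need only the equation, the schedule and speed in m/min.

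A reader might go further and infer that the randomised CRF comparison is invalid. The article does not support that: with the same stopping criterion at both visits the score still carries information on submaximal fitness. What it cannot supply is a mean and SD of VO2 max for the definitive trial's power calculation.

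**What to change.** Leave the stopping rules as they are and correct the derived variable in one of two ways.

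(a) **Extrapolate.** For each participant, fit the line of measured VO2 (or workload) on heart rate over the submaximal stages and project it to age-predicted HRmax, using the same HRmax at both visits. The price is error in predicted HRmax and instability when few stages are completed.

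(b) **Rename.** Keep the equation, state that terminal speed and grade (with units) are entered, call the outcome *estimated VO2 at test termination*, and do not use it as VO2 max when sizing the definitive trial.

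Under either option, record the stopping reason at each visit and report it by arm. Add a sensitivity analysis using measured VO2 or workload at a fixed submaximal heart rate, or one restricted to participants with the same stopping criterion at both visits. If the full protocol already extrapolates, say so in the article.

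The cost is the redefinition or relabelling of one variable, one extra recorded item and one sensitivity analysis. The data come from the test already planned, so no new test or equipment is needed.

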##### Subjective self-report questionnaires

All participants will be issued a combined set of valid and reliable self-reported outcome questionnaires detailed in Table 2. These will take approximately 30 min to complete. The participant will be given the option to complete these surveys online or in paper format. Participants who wish to complete the questionnaires online will be sent an email with the link and the option to complete them either in advance or following their appointment in ISH. The self-reported measures are in line with the core outcome set for weight management interventions in adults with obesity [63, 64]. In addition, pain was included as an outcome given the strong association between chronic pain and obesity and the potential impact of pain on exercise adherence [65, 66].

**Table 2 Tab2:** Primary and secondary outcome measures

Outcomes	Measure(s)
Anthropometrics	BMI, body weight, % body fat, waist circumference, fat-free mass, lean mass, waist hip ratio, height
Cardiorespiratory Fitness	Predicted VO_2_ max
Muscle strength	5RM bench press, leg dynamometry, grip strength
Pain	Brief Pain Inventory (Short form)
Health-related quality of life	EuroQol-5D-5L (EQ-5D-5L) questionnaire
Mood	Patient Health Questionnaire-9 (PHQ-9)
Self-reported physical activity & sedentary time	International Physical Activity Questionnaire (IPAQ) (Short Form)
Sleep	Pittsburgh Sleep Quality Index

#### Randomisation

A member of the research team, with no involvement in the baseline/follow-up assessments or delivery of the interventions will independently assign all consenting participants a unique number using a random number table. Another independent investigator will utilise a computer-generated random allocation sequence to allocate numbered participants to each of the trial arms. Participants will be block randomised in blocks of four. The trial coordinator ([name]) will then contact this independent investigator to obtain each participant’s random group allocation.

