## Methods

### Quantitative study

#### Trial design

This four-arm parallel pilot study has been approved by University College Dublin (UCD) Human Research Ethics Committee (LS-21-59-[name]) and will be reported in line with the Consolidated Standards of Reporting Trials (CONSORT) guidelines extension for randomised pilot and feasibility trials [48] and the Standard Protocol Items: Recommendations for Interventional Trials (SPIRIT) [49]. Following initial screening, the participants will be randomised with an allocation ratio of 1:1:1:1 into one of the three time-matched exercise modes or control (Figs. 1 and 2).Aerobic: progress to 150 min/week of continuous aerobic exercise at 75–80% HRRResistance training: progress to 150 min/week of 3–6 × 12 reps of resistance exercise at 75–80% 1-RMCombined training: progress to a 50:50 split of combined aerobic (75–80% HRR) and resistance (3–6 × 12 reps, 3 exercises at 75–80% 1RM) training for 150 min/weekControl: non-exercise group (participants to maintain baseline physical activity levels)

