#### Participants

Participants will be recruited using a flyer which will be distributed in UCD internal networks, on social media platforms and in local areas (clinics, health centres, pharmacies) and shared with the chairperson of the Irish Coalition for People Living with Obesity (ICPO) with its members. Interested participants will be encouraged to contact the trial coordinator ([name]) who will complete eligibility screening over the telephone using the criteria detailed in Table 1 to evaluate a participant’s eligibility and individual safety for starting an exercise programme using the Physical Activity Readiness Questionnaire for Everyone (PAR-Q+). If screened as eligible, potential participants will receive the study information sheet and consent form by email or by post (preferred method). All consenting participants will be invited to ISH for baseline assessment a minimum of seven days later (cooling off period) (Fig. 2).

**Table 1 Tab1:** Eligibility criteria for inclusion in trial

Criterion	Characteristics of eligible participants
1	Female aged 18-50 years at time of consent
2	Have a Body Mass Index (BMI) ≥ 30 kg m^−2^ and /or a waist circumference > 88 cm
3	Are currently physically inactive (exercising less than 150 min/week)
4	Have not undergone weight loss surgery or another surgery in the past 3 months
5	Not pregnant (or within 6 months post-pregnancy) or lactating
6	Do not have a significant mental illness or cognitive deficits
7	Are not participating in another trial (exercise-based or targeting weight-loss) at time of consent
8	Are not contraindicated or no clinician (i.e. GP) has advised them against exercising (i.e. chest pain during activity or at rest, severe hypertension etc.)
9	Do not have an unstable cardiovascular, respiratory, renal or hepatic condition

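### One disclosed block size of four for four arms lets the enrolling coordinator deduce every fourth allocation, if blocks fill in enrolment order

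*Protocol article*

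**What the plan says.** All references are to the protocol article.

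- **Arms and ratio (Trial design):** "participants will be randomised with an allocation ratio of 1:1:1:1 into one of the three time-matched exercise modes or control".
- **Block size (Randomisation):** "Participants will be block randomised in blocks of four". No other size, no variation and no stratification factor is given.
- **Sequence (Randomisation):** one uninvolved team member gives each consenting woman a number from a random number table. A second independent investigator holds the computer-generated sequence. The trial coordinator "will then contact this independent investigator to obtain each" woman's arm.
- **Coordinator's other duties:** the coordinator is the person "who will complete eligibility screening over the telephone" (Participants), and also meets women at the baseline and consent visit (Baseline assessment).
- **Blinding:** participants cannot be blinded, nor can assessors and instructors once the intervention starts. Assessors and instructors are kept out of allocation. The coordinator is not mentioned in that safeguard.
- **Questionnaires:** women who choose the online forms have the "option to complete them either in advance or following their appointment in ISH".
- **Sample size:** "we aim to recruit 60 participants for this pilot study to inform the power analysis for a full-scale RCT".

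**The concern.** When the block size equals the number of arms, each block is a permutation of the four arms. Anyone who knows the earlier allocations in a block knows what is left. The independent investigator conceals the list, but cannot stop someone deducing the next arm from allocations already disclosed.

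The coordinator hears every allocation and also handles screening and the baseline visit, at a single site. Sixty women over the 16 months from September 2021 to December 2022 is 60/16 = 3.75 a month, so earlier allocations will usually be known before later women enter. The cooling-off period before baseline has a minimum of seven days and no stated maximum, so the order of entry can shift. A person who expects control next could, even without intending to, bring one woman forward and hold another back.

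That could alter the make-up of the arms. Retention, attendance and adherence are feasibility outcomes that depend on motivation, and the between-group difference in cardiorespiratory fitness is meant to inform whether a full trial is worth pursuing. A predictable scheme might also be carried into that trial.

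A secondary question is whether some self-reported baselines (pain, quality of life, mood, activity, sleep) could be given after a woman knows her arm. Change from baseline is analysed for these outcomes.

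**Working it through.** **1. The planned 60.** The plan says "a sample size calculation for a definitive RCT indicates that we would need to recruit 484 participants", takes about 10% of that for the pilot and allows for 20% attrition. 0.10 × 484 = 48.4, and 48.4/(1 − 0.20) = 60.5. Starting from 48, 48/0.80 = 60. The stated 60 is reproduced. The 484 cannot be rebuilt, because its inputs are not given. Number of blocks: 60/4 = 15.

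**2. Blocks filled in enrolment order, earlier allocations known.** The chance of naming the next arm is one over the number of arms left in the block:

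| Place in block | Chance of a correct guess |
|---|---|
| 1 | 1/4 |
| 2 | 1/3 |
| 3 | 1/2 |
| 4 | 1 |

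Mean = (1/4 + 1/3 + 1/2 + 1)/4 = 25/48 = 52.1%, against 25% by chance. Over 60 women that is 60 × 25/48 = 31.25 correct guesses, against 15. Fifteen allocations are certain and 15 more are even bets between two arms.

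**3. Control versus any exercise arm.** This status is certain once control has appeared in the block, or at the last place. By place the probabilities are 0, 1/4, 1/2 and 1. The mean is 1.75/4 = 43.75%, or 26.25 of 60.

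**4. If the numbering scrambles the order.** Suppose the random-number-table numbers index a ready-made list, so that enrolment order no longer follows block position. This was modelled as drawing without replacement from 15 places per arm, with the guesser naming the arm with most places left. In 1,500 simulated trials, 34.6% of guesses were correct and 1.3 allocations per trial were certain.

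**5. Alternatives, filled in enrolment order.** The fixed-block guess rates are exact. The varying-block rates come from 1,500 simulated trials of 60 women, with the guesser naming the arm least allocated so far.

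| Scheme | Correct guesses | Certain allocations |
|---|---|---|
| Fixed 4, known | 52.1% | 15 of 60 |
| Fixed 8, known | 47.0% | about 8 of 60 (simulated) |
| Fixed 12, known | 44.1% | at least 60/12 = 5 |
| Varying 4/8, undisclosed | about 48.5% | largely removed |
| Varying 4/8/12, undisclosed | about 46.1% | largely removed |

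The entries for varying blocks in the last column are by reasoning, not count. Three different arms in a row no longer fix the fourth, because the block may be longer than four. Someone who learned the set of sizes could still meet an occasional forced allocation.

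**6. Questionnaires.** No arithmetic applies. One section allows online forms after the appointment. The Randomisation section requires consent before numbering, and Trial design places randomisation after initial screening. None of the text shown makes return of the forms a condition for releasing the allocation. None of it says that forms completed after the visit are completed after allocation.

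**The case against.** **The certainty is conditional.** Numbers come from a random number table before numbered women are allocated. If those numbers set the place on the list, the coordinator gains much less: about 35% correct and about one certain allocation. This stands, and the figures must be given as a range. Filling in enrolment order remains the ordinary reading of block randomisation.

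**The sequence is held independently.** True, and a reader might wrongly infer that the coordinator can see the list. The documents do not support that. The weakness is deduction from past allocations only, and nothing suggests that anyone has acted on it.

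**The questionnaire point rests on silence.** A reader might infer that the plan allows baseline forms after allocation, or randomises straight after the telephone screen. Neither is supported. After the appointment is not stated to mean after allocation. Consent is signed at the baseline visit before any procedure, and only consenting women are numbered. The flow and schedule figures, which may show the order, are not available, and a condensed article may leave such detail to the full protocol. Only a precaution survives.

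**The harm is limited.** Feasibility is the main outcome, it is reported as percentages with no planned between-arm test, and the pilot is not powered for group differences. Eligibility is set by Table 1, and control women are later offered a programme of their choice, which weakens any motive to steer. All this lowers the stakes but does not remove the predictability.

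**The gain is modest.** Falling from 52% to 46% is a small change, and a known fixed block of 12 does slightly better on that measure. The main benefit of varying, undisclosed sizes is the loss of certain allocations.

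**Conclusion.** The point holds in a conditional form. A single disclosed block of four, for four arms at equal ratio, makes 15 of 60 allocations deducible and raises correct guessing to 52.1% from 25%. This assumes that blocks fill in enrolment order and that the coordinator keeps track of earlier allocations. If the numbering step scrambles the order, the figures are about 35% and about one certain allocation. The Randomisation section leaves this open and should settle it.

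This is a worthwhile and inexpensive improvement to a stated rule. It is not a ground for calling the pilot invalid, and it is not evidence of biased enrolment. Questionnaire timing is a potential risk only and carries much less weight.

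**What to change.** 1. For the remaining allocations, use permuted blocks of randomly varying size (for example 4, 8 and 12). The sizes should be known only to the independent investigator and kept out of documents that trial staff can read.
2. State whether blocks fill in order of enrolment or by the random-number-table number.
3. As a secondary safeguard, add one sentence: the independent investigator releases an allocation only once all baseline measures, including every questionnaire, are logged as complete.

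The cost is a regenerated list for the women still to be randomised, one or two procedural sentences, and a possible final imbalance of a few participants between arms. If recruitment has finished, the list cannot be changed. The report should then say how blocks were filled and whether baseline questionnaires preceded allocation, and should note predictability as a limitation.
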